### Interventions

Investigational and control products. All participants will receive a once-daily three-in-one PN admixture corresponding to their assigned group. The investigational product is a high-protein (amino acid–enriched) peripheral PN formulation and the control product is a conventional peripheral PN formulation (Winuf A-plus peri and Winuf peri, respectively; JW Pharmaceutical, Seoul, Republic of Korea). Both products contain an identical lipid emulsion (a four-oil mixture of soybean oil, medium-chain triglycerides, olive oil, and fish oil at 30:25:25:20 by lipid weight, with an ω-6:ω-3 ratio of 2.1:1), so that the principal compositional difference between the two arms is the relative content of amino acids and dextrose. The investigational product delivers approximately 19% more amino-acid–derived nitrogen per millilitre and a correspondingly lower non-protein calorie-to-nitrogen (NPC/N) ratio than the control product (84 vs 109, respectively). Detailed compositional information is provided in Table 2. Because the two products differ simultaneously in amino-acid content, dextrose content, NPC/N ratio, electrolytes, osmolarity, and required infusion volume, the investigational arm represents a composite intervention (higher protein, lower carbohydrate, and lower NPC/N ratio); the expected daily delivered amounts of amino acids, nitrogen, glucose, and lipid for both arms at the scheduled coverage on each intervention day are provided in S4 Table, and this composite nature is considered in the interpretation of secondary outcomes.

**Table 2 pone.0355677.t002:** Composition of control and investigational peripheral parenteral nutrition products.

Component	Unit	Control (Winuf peri, conventional formulation)	Investigational (Winuf A-plus peri, amino acid–enriched)
**Composition per mL**			
Amino acids	mg/mL	31.5	37.4
Glucose (anhydrous)	mg/mL	70.7	64.4
Lipid	mg/mL	29.9	27.8
Nitrogen	mg/mL	5.21	6.17
Total energy	kcal/mL	0.69	0.67
**Energy and protein quality**			
Glucose: lipid energy ratio	%	50: 50	50: 50
Non-protein calorie-to-nitrogen ratio (NPC/N)	—	109	84
Essential amino acids/ total amino acids	%	45.3	45.3
Branched-chain amino acids/ total amino acids	%	19	19.1
**Lipid emulsion composition**			
Soybean oil	% of lipid	30	30
Medium-chain triglycerides	% of lipid	25	25
Olive oil	% of lipid	25	25
Fish oil	% of lipid	20	20
ω-6: ω-3 fatty acid ratio	—	2.1: 1	2.1: 1
**Electrolytes (per L)**			
Sodium (Na⁺)	mmol/L	25.3	29.9
Potassium (K⁺)	mmol/L	18.9	22.5
Magnesium (Mg²⁺)	mmol/L	3.16	3.75
Calcium (Ca²⁺)	mmol/L	1.59	1.88
Phosphate (PO_4_^3-^)	mmol/L	8.24	9.22
Zinc (Zn²⁺)	mmol/L	0.025	0.028
Chloride (Cl^-^)	mmol/L	34.6	41.1
Acetate (CH_3_COO^-^)	mmol/L	13	15.4
Sulfate (SO_4_²^-^)	mmol/L	3.18	3.77
**Physical properties**			
Osmolarity	mOsm/L	850	892
**Reference single-bag values (standard size)**			
Bag volume	mL	1085	1089
Amino acids	g	34.2	40.7
Glucose (anhydrous)	g	76.7	70.1
Lipid	g	32.4	30.3
Nitrogen	g	5.65	6.72
Total energy	kcal	751	730
Non-protein calories	kcal	614	567
**Manufacturer-stated maximum daily delivery (at the labelled maximum volume of 40 mL/kg/day)**			
Amino acids	g/kg/day	1.26	1.49
Glucose	g/kg/day	2.83	2.57
Lipid	g/kg/day	1.2	1.11
Total energy	kcal/kg/day	27.7	26.8
**Trial-protocol caloric target (back-calculated from 20 kcal/kg/day)**			
Resulting nitrogen delivery	g/kg/day	0.151	0.185
Required volume as % of manufacturer maximum (40 mL/kg/day)	%	73	75

Per-mL values are calculated from manufacturer specifications. Both products are three-in-one peripheral parenteral nutrition formulations manufactured by JW Pharmaceutical (Seoul, Republic of Korea). Bag sizes available at the participating institution: 1,085 mL and 2,020 mL for the control product, and 1,089 mL and 1,452 mL for the investigational product. The lipid emulsion composition is identical in the two products, isolating amino-acid and dextrose content as the principal compositional differences. The manufacturer-stated maximum daily volume of 40 mL/kg/day defines a regulatory ceiling rather than the trial-protocol dose. In the PROGAIN trial, the daily caloric target is back-calculated from a permissive hypocaloric target of 20 kcal/kg/day (using actual body weight when BMI < 25 and ideal body weight when BMI ≥ 25, with ideal body weight defined as height² × 23 in metres-squared and kilograms), and the required PN volume is delivered using a volumetric infusion pump. Abbreviations: BMI, body mass index; NPC/N, non-protein calorie-to-nitrogen ratio.

**Caloric target and dose calculation.** The daily caloric target during the intervention period is set at 20 kcal/kg/day, in keeping with current evidence supporting permissive hypocaloric feeding to avoid perioperative overfeeding. Body weight used for dose calculation is determined by body mass index (BMI): actual body weight is used for participants with BMI < 25 kg/m², and ideal body weight—calculated as height (m)² × 23 (a reference body-mass index of 23 kg/m², consistent with recommendations for Asian populations) [21], applied to both sexes—is used for those with BMI ≥ 25 kg/m². The required daily PN volume is back-calculated from the caloric target using the energy density of the assigned product (0.69 kcal/mL for the control and 0.67 kcal/mL for the investigational product), rounded to the nearest 1 mL, and delivered through a volumetric infusion pump. The calculated daily volume is not expected to exceed the manufacturer-stated maximum of 40 mL/kg/day. For a 75-kg participant, the control formulation delivers approximately 68 g of amino acid per day (0.9 g/kg) and the high-protein formulation approximately 84 g (1.1 g/kg); detailed examples are provided in S2 and S3 Tables. These amino-acid amounts represent PN-only delivery; the total protein supply (oral plus parenteral) that forms the basis of the nitrogen-balance calculation is higher, and the between-arm difference should be interpreted as a difference in PN-delivered rather than total protein.

**Stepwise PN delivery schedule.** PN is administered through a peripheral intravenous line; central venous access is not required. Peripheral access was chosen to avoid the infection and thrombosis risks of central venous catheterisation, consistent with the broader Enhanced Recovery After Surgery (ERAS) principle of minimizing invasive perioperative procedures. PN is initiated on the preoperative day (preoperative day −1; POD −1), withheld on the day of surgery (POD 0) because of perioperative anaesthetic and surgical considerations, and resumed from POD 1 through POD 5, for a total of six administration days. The PN dose on each day is delivered as a fixed proportion of the daily caloric target, decreasing stepwise as anticipated oral intake advances: 80% on POD −1, 100% on POD 1, 60% on POD 2 and POD 3, and 50% on POD 4 and POD 5. The stepwise schedule is summarized in Table 3.

**Table 3 pone.0355677.t003:** Stepwise perioperative parenteral nutrition delivery schedule.

Postoperative day	Oral diet stage	Anticipated mean oral energy intake (kcal/day)*	Scheduled PN coverage (% of daily caloric target)
POD −1	Preoperative oral carbohydrate loading	≈200 (per protocol)	80%
POD 0	Surgery — nil per os	—	PN withheld
POD 1	Sips of water	—	100%
POD 2	Post-gastrectomy liquid diet	≈350	60%
POD 3	Post-gastrectomy early soft diet	≈315	60%
POD 4–5	Post-gastrectomy soft diet	≈820	50%

PN, parenteral nutrition; POD, postoperative day. *Anticipated oral energy intake for POD 2 through POD 5 is derived from a 1-year retrospective audit of post-gastrectomy hospital meal intake at the participating institution (August 2024 – July 2025; n = 92, 160, and 102 measurements for the liquid, early soft, and soft diet stages, respectively); detailed values are provided in S1 Table. The daily caloric target is set at 20 kcal/kg/day, calculated using actual body weight when BMI < 25 kg/m² and ideal body weight (height [m]² × 23) when BMI ≥ 25 kg/m². The corresponding daily PN volume is back-calculated from the assigned product’s energy density (0.69 kcal/mL for the control and 0.67 kcal/mL for the investigational product), rounded to the nearest 1 mL, and delivered through a volumetric infusion pump. Preoperative oral carbohydrate loading is provided in two 200-mL servings on POD −1 of a commercially available carbohydrate-rich nutritional supplement (Nucare NoenPiO; Daesang Wellife, Republic of Korea), to maintain preoperative carbohydrate intake before the institutional mandatory fasting period (initiated from the evening of POD −1 owing to indocyanine green injection for sentinel lymph node mapping), in keeping with the underlying Enhanced Recovery After Surgery Society principle of avoiding prolonged preoperative fasting.

**Rationale for the stepwise schedule.** The proportional schedule was calibrated against an institutional 1-year retrospective audit (August 2024 – July 2025) of measured meal-by-meal oral intake yielding 354 stage-level intake measurements in post-gastrectomy inpatients at the participating center. Mean oral energy intake was approximately 350, 315, and 820 kcal/day for the post-gastrectomy liquid, early soft, and soft diet stages, respectively (S1 Table); the slightly lower energy at the early soft stage than the liquid stage reflects carbohydrate-drink supplementation of the liquid-diet stage and is also present in the standardized provided diet. Combined with PN coverage of 60%, 60%, and 50% of the daily caloric target, the schedule maintains total daily caloric delivery within approximately 80–120% of the 20 kcal/kg/day target across the body weight range typically encountered in elective gastrectomy (S2 Table), while reducing the risk of perioperative overfeeding.

**Concomitant nutritional care.** All participants follow the institutional standardized perioperative nutrition pathway, which is aligned with current ERAS Society recommendations [22] and is delivered by a multidisciplinary NST comprising a clinical pharmacist, a dietitian, a ward nurse, and an attending physician. In keeping with the institutional preoperative pathway, which requires fasting from the evening of POD −1 owing to indocyanine green injection for sentinel lymph node mapping, preoperative oral carbohydrate loading is administered on POD −1 in two 200-mL servings (approximately 200 kcal in total) of a commercially available carbohydrate-rich nutritional supplement to maintain adequate preoperative carbohydrate intake before the mandatory fasting period, in keeping with the underlying ERAS Society principle of avoiding prolonged preoperative fasting. Postoperatively, oral intake advances stepwise: sips of water from POD 1, a post-gastrectomy liquid diet on POD 2, a post-gastrectomy early soft diet on POD 3, and a post-gastrectomy soft diet on POD 4 and POD 5, advanced as tolerated. Daily oral intake is recorded meal by meal in 25% increments using a study-specific intake form (S1 File), from which oral energy and protein intake are calculated. The NST and the investigators may adjust supplementary fluids and electrolytes outside the assigned PN as clinically indicated; the assigned PN itself is not substituted with another commercial PN product during the intervention period. No oral nutritional supplements beyond the protocol-specified standardized perioperative diet are permitted during the intervention period; all oral intake, including the standardized supplement components of the diet, is recorded on the meal-by-meal intake form and included in the oral-protein term of the nitrogen-balance calculation.

**Monitoring and dose modification.** During the intervention period, blood glucose, serum electrolytes, hepatic and renal function tests, body weight, and urine output are monitored daily by the NST. The assigned PN may be temporarily withheld or reduced at the investigator’s discretion for predefined safety triggers, including blood glucose ≥250 mg/dL, clinically significant hepatic enzyme elevation, or mild to moderate infusion-site reactions. Permanent discontinuation of the allocated PN with withdrawal from the per-protocol population is reserved for severe intra- or postoperative complications — including anastomotic leak, bacteremia, or fungemia — and for severe infusion-related events that preclude further PN (e.g., refractory infusion-site pain or phlebitis); in such cases the allocated PN is discontinued at the discretion of the treating clinician, and the participant is retained in the intention-to-treat population and flagged for sensitivity analysis. Any modification or discontinuation of the assigned regimen, together with the reason, is documented on the case report form. Adherence to the allocated intervention is summarized as the proportion of planned PN doses received and the cumulative volume of allocated PN administered during POD −1 through POD 5.

### Outcomes

**Primary outcome.** The primary outcome is the nitrogen balance on POD 5, expressed in grams per day. Nitrogen balance is calculated using the standard simplified clinical formula: N balance (g/day) = [24-hour oral protein intake (g) ÷ 6.25 + 24-hour parenteral nitrogen delivered (g)] − (24-hour urinary urea nitrogen (g) + 4), where oral protein is converted using the divisor 6.25 (protein contains approximately 16% nitrogen by weight), parenteral nitrogen is derived directly from the product-specific nitrogen content (Table 2; 5.21 mg/mL for the control and 6.17 mg/mL for the investigational product) multiplied by the administered volume rather than from the amino-acid mass, and the constant 4 g accounts for non-urinary nitrogen losses through the integument and the gastrointestinal tract [23,24]. POD 5 was selected as the primary endpoint because previous prospective studies of perioperative protein supplementation in upper gastrointestinal cancer surgery have used assessment windows between POD 3 and POD 7, with POD 5 marking the transition from the catabolic phase that peaks within the first 48–72 hours after surgery to the early anabolic recovery phase [13,14,16]. The 24-hour urinary urea nitrogen collection is performed over POD 5 (00:00–24:00) by self-voided collection, since catheters are removed early under enhanced recovery; participants receive standardized instruction, and collection times and total urine volume are recorded as a completeness check, with incomplete collections flagged and handled per the missing-data plan (all participants remain hospitalized through POD 5). Participants with significant non-urinary gastrointestinal losses (high-output drainage, prolonged nasogastric aspiration, vomiting, or anastomotic leak) are flagged for sensitivity analysis. As limitations, the fixed 4 g constant does not capture gastrointestinal losses and completeness was not verified by creatinine; because both apply similarly across the randomized arms, residual error is expected to be non-differential.

**Secondary outcomes — nitrogen balance on POD 3.** To characterize the early trajectory of nitrogen metabolism, nitrogen balance is additionally assessed on POD 3 as a secondary outcome.

**Secondary outcomes — nutritional status.** Secondary nutritional outcomes include the skeletal muscle index measured at the third lumbar vertebral level on abdominopelvic computed tomography; composite nutritional and inflammatory–nutritional indices comprising the Nutritional Risk Screening 2002 (NRS-2002), GLIM criteria, Prognostic Nutritional Index (PNI), C-reactive protein–to-albumin ratio (CAR), and modified Glasgow Prognostic Score (mGPS); serum nutritional biomarkers (albumin, prealbumin, total protein); and longitudinal changes in body weight, body composition assessed by multifrequency segmental bioelectrical impedance analysis (InBody 770; InBody Co., Ltd., Seoul, Republic of Korea), and handgrip strength assessed by hand dynamometry.

**Secondary outcomes — glycemic control.** Postoperative glycemic outcomes comprise the proportion of participants with any blood glucose ≥180 mg/dL during POD 0 through POD 5, stratified by baseline diabetes status, together with the cumulative insulin requirement during the same period. Because the investigational formulation also delivers less carbohydrate, these glycemic outcomes partly reflect the compositional difference in carbohydrate load and are interpreted accordingly.

**Secondary outcomes — postoperative complications.** Postoperative complications occurring within 30 days after surgery are classified using the Clavien–Dindo classification. Specific complications captured include surgical site infection; pneumonia; delayed gastric emptying; and anastomotic leak.

**Secondary outcomes — functional recovery.** Functional recovery milestones aligned with the institutional ERAS pathway include time to first defecation, time to tolerate ≥50% of a soft diet for 24 hours, time to independent corridor ambulation, and length of postoperative hospital stay. Patient-reported recovery outcomes are assessed at POD 14, 1 month, 3 months, 6 months, and 12 months, and encompass oral intake (proportion relative to preoperative volume and meal frequency), early satiety, appetite loss, gastrointestinal symptoms (nausea, vomiting, dumping, reflux, diarrhoea, constipation), oral nutritional supplement use, and habitual physical activity. Clinical events—including emergency department visits, readmissions, and interventions—are captured through 12 months.

**Safety outcomes.** Adverse events, adverse drug reactions, and serious adverse events are recorded throughout the intervention and follow-up period, with investigator-assessed causality and severity. Predefined laboratory safety monitoring includes aspartate and alanine aminotransferase, blood urea nitrogen, serum creatinine, blood glucose, and serum electrolytes. Serious adverse events are reported within 24 hours to the manufacturer’s pharmacovigilance team in accordance with regulatory requirements. Infusion-site reactions are graded using the Visual Infusion Phlebitis score [25], and peripheral catheters are re-sited according to standard nursing practice; hyperglycemia (blood glucose ≥250 mg/dL) is managed with protocol-directed insulin. No formal data and safety monitoring board is convened, given the single-centre design, the short six-day intervention, and the use of two regulatory-approved PN products with established safety profiles; safety is overseen by the principal investigator with periodic institutional review board review.

Detailed measurement methods, timepoints, and prespecified statistical analyses for all primary and secondary outcomes are provided in Table 4. The full schedule of study assessments at each visit is summarized in Fig 1 (SPIRIT schedule).

**Table 4 pone.0355677.t004:** Primary, secondary, and safety outcomes with measurement methods, timepoints, and statistical analysis.

Outcome	Measurement/ definition	Timepoint(s)	Statistical analysis
**Primary outcome**			
Nitrogen balance on postoperative day 5	N balance (g/day) = [oral protein (g) ÷ 6.25 + parenteral nitrogen delivered (g)] − (urinary urea nitrogen (g) + 4); parenteral nitrogen is derived from the product-specific nitrogen content (Table 2) and administered volume [23,24]	POD 5	Two-sample t-test (or Wilcoxon rank-sum if non-normal); intention-to-treat as primary analysis
**Secondary outcomes — Nutritional status**			
Nitrogen balance trajectory	Same formula as the primary outcome, applied at the early postoperative time point	POD 3	Two-sample t-test or Wilcoxon rank-sum
Sarcopenia index	Skeletal muscle index measured at the third lumbar vertebral level on abdominopelvic computed tomography (cm²/m²)	Baseline, 3, 6, 12 months	Paired t-test (within-group); two-sample t-test (between-group); Chi-square or Fisher’s exact (sarcopenia incidence)
Nutritional risk and inflammatory–nutritional indices	Nutritional Risk Screening 2002 (NRS-2002), Global Leadership Initiative on Malnutrition (GLIM) criteria, Prognostic Nutritional Index (PNI), C-reactive protein–to-albumin ratio (CAR), modified Glasgow Prognostic Score (mGPS)	POD −1, POD 5, 1, 3, 6, 12 months	Two-sample t-test or Wilcoxon rank-sum (continuous); Chi-square or Fisher’s exact (categorical)
Serum nutritional biomarkers	Albumin, prealbumin, total protein	POD −1, POD 5; albumin/total protein additionally at 1, 3, 6, 12 months	Paired t-test (within-group); two-sample t-test (between-group)
Body weight, body composition, handgrip strength	Body weight; multifrequency segmental bioelectrical impedance analysis (InBody 770; InBody Co., Ltd., Seoul, Republic of Korea); handgrip dynamometry (kg)	Body weight: POD −1 and 14 days, 1, 3, 6, 12 months; InBody and handgrip: POD −1, 1, 6, 12 months	Linear mixed-effects model for repeated measures (random intercept per participant; fixed effects for treatment, time, and treatment × time interaction); between-group differences reported with 95% confidence intervals

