**Safety outcomes**			
Adverse events, adverse drug reactions, and serious adverse events	Any adverse event, adverse drug reaction (per investigator’s causality assessment), or serious adverse event recorded throughout the intervention and follow-up period	Through 12 months	Descriptive (number of participants, events, incidence proportion); Chi-square or Fisher’s exact test for between-group comparison
Laboratory safety	Aspartate and alanine aminotransferase, blood urea nitrogen, serum creatinine, glucose, electrolytes	POD −1, POD 3, POD 5, 1, 3, 6, 12 months	Descriptive summary; between-group comparison at each timepoint

All analyses will be performed on the intention-to-treat population, with per-protocol analysis as a sensitivity analysis. Two-sided α = 0.05 will be used throughout. The single primary endpoint is the sole confirmatory analysis. The two key secondary endpoints — POD 3 nitrogen balance (reported with the nitrogen balance trajectory) and the early change in serum prealbumin, defined as the change from the preoperative (POD −1) baseline to POD 5 — are controlled for family-wise error at 0.05 by the Holm procedure, independently of the primary result; all other secondary outcomes are exploratory and reported with 95% confidence intervals without multiplicity adjustment. For the primary endpoint, genuine missing data are handled by multiple imputation under the missing-at-random assumption as the primary approach, with complete-case analysis as a sensitivity analysis and a delta-adjusted (tipping-point) analysis under missing-not-at-random assumptions. Full specifications are given in the dated statistical analysis plan (SAP v1.0, 21 July 2026). Abbreviations: APCT, abdominopelvic computed tomography; CAR, C-reactive protein–to-albumin ratio; GLIM, Global Leadership Initiative on Malnutrition; mGPS, modified Glasgow Prognostic Score; NRS-2002, Nutritional Risk Screening 2002; ONS, oral nutritional supplement; PNI, Prognostic Nutritional Index; POD, postoperative day.

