### Sample size

The primary outcome is the nitrogen balance on POD 5, expressed in grams per day, compared between the two arms. The sample size calculation is based on a two-sample t-test of independent means. In the absence of a directly comparable randomized trial of high-protein versus conventional PN in patients undergoing gastric cancer surgery, the assumed effect size and variability were derived from related studies of postoperative nitrogen balance under modified protein and amino-acid support [13,14] and from clinical considerations of the smallest between-group difference that would be regarded as clinically meaningful in this population. A between-group mean difference of 3 g/day in postoperative nitrogen balance was assumed, with a common standard deviation of 5 g/day. Using a two-sided significance level of 0.05 and statistical power of 80%, the minimum required sample size is 44 participants per arm (88 participants in total). Anticipating a combined withdrawal, protocol non-completion, or missing primary outcome rate of approximately 20%, the planned enrollment is increased to 55 participants per arm, giving a total target enrollment of 110 participants. The 20% inflation is an allowance for missingness of the POD 5 primary outcome — incomplete 24-hour collection, early events, PN discontinuation, or death before POD 5 — rather than attrition during the 12-month follow-up; it is a conservative estimate consistent with the completeness typically achievable for a fixed-day metabolic endpoint and with attrition reported in comparable post-gastrectomy nutrition trials [26,27]. Because scheduled PN coverage on POD 5 is 50%, the between-arm difference in delivered nitrogen on the primary-endpoint day is approximately 1.0–1.2 g/day, with a cumulative difference of roughly 8 g over the six-day intervention; the assumed 3 g/day balance difference therefore exceeds the single-day intake difference and, if observed, would indicate a genuine difference in nitrogen retention rather than intake alone. The sensitivity of statistical power to the assumed effect size and standard deviation is summarized in S5 Table.

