### Statistical analysis

**Analysis populations.** All efficacy analyses are performed in the intention-to-treat (ITT) population, comprising all randomized participants analyzed in the group to which they were allocated. The per-protocol population is defined as participants who completed the planned PN intervention through POD 5, received at least 90% of the planned cumulative allocated PN volume or amino acid dose, completed the POD 5 nitrogen balance assessment, and had no prespecified major protocol deviations; this population will be used for sensitivity analyses of the primary and key secondary outcomes. The safety population comprises all participants who received at least one administration of allocated PN.

**Primary analysis.** The primary outcome is compared between the investigational and control arms using a two-sample t-test, with the between-group mean difference reported with a 95% confidence interval; the Wilcoxon rank-sum test is used as a sensitivity analysis if distributional assumptions are clearly violated. In a prespecified adjusted analysis, POD 5 nitrogen balance is modelled by analysis of covariance (ANCOVA) with treatment arm as the factor and extent of gastric resection and baseline nutritional status as covariates.

**Mechanistic analyses of the primary endpoint.** To separate the arithmetic and metabolic components of the endpoint, prespecified mechanistic analyses compare between arms (a) total nitrogen intake, (b) urinary urea nitrogen excretion, and (c) net nitrogen retention on POD 5, and evaluate nitrogen-utilization efficiency (net retention relative to delivered nitrogen), and, in an exploratory analysis, adjust the primary endpoint for delivered nitrogen as a covariate. Because delivered nitrogen is a post-randomization variable largely determined by treatment allocation, adjustment for it cannot by itself causally separate nitrogen delivery from nitrogen utilization; these analyses are exploratory and descriptive, use already-recorded variables, and are reported with 95% confidence intervals as hypothesis-generating without causal claims. The partial dependence of nitrogen balance on nitrogen intake is acknowledged as a limitation that these analyses are designed to characterize.

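### The Holm-controlled prealbumin endpoint is tested by an unadjusted t-test on change, although ANCOVA on the collected baseline would be more efficient and need no new data

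*Protocol article*

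**What the plan says.** The outcomes section of the protocol article points to Table 4 for the prespecified analyses of all primary and secondary outcomes. The Table 4 row for serum nutritional biomarkers (albumin, prealbumin, total protein) gives "Paired t-test (within-group); two-sample t-test (between-group" as the analysis and "POD −1, POD 5; albumin/total protein additionally at 1, 3, 6, 12 months" as the time points, so a baseline prealbumin value is collected.

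The Table 4 footnote names two key secondary endpoints, POD 3 nitrogen balance and "the early change in serum prealbumin, defined as the change from the preoperative (POD −1) baseline to POD 5". These "are controlled for family-wise error at 0.05 by the Holm procedure, independently of the primary result". Row and footnote together make the between-arm test for prealbumin a two-sample t-test on the change score.

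The only ANCOVA described is in the Statistical analysis section, for the primary outcome: "POD 5 nitrogen balance is modelled by analysis of covariance (ANCOVA) with treatment arm as the factor", with extent of resection and baseline nutritional status as covariates. For further detail the footnote says: "Full specifications are given in the dated statistical analysis plan (SAP v1.0, 21 July 2026". That plan is not at hand.

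**The concern.** A t-test on change fixes the coefficient of the baseline value at 1. ANCOVA estimates it. Where the true slope differs from 1, the change score leaves avoidable variance in the estimate, and any chance baseline difference between arms is passed on to the estimated effect.

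This matters more here than for an exploratory outcome. Prealbumin has family-wise error control, so if it has the smaller of the two p-values it is tested at 0.05/2 = 0.025. The sample size was set for nitrogen balance alone, so the article shows no power reserve for prealbumin. The Randomization section also justifies unstratified allocation partly by controlling baseline nutritional status in the analysis. Prealbumin is a nutritional marker, yet its own baseline is not used in its own test.

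A lesser matter is that Table 4 prints the within-group paired tests beside the between-group test without stating their role. They measure change after surgery within an arm and do not compare the arms.

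**Working it through.** **The plan's own figure.** The Sample size section states: "A between-group mean difference of 3 g/day in postoperative nitrogen balance was assumed, with a common standard deviation of 5 g/day", and then "Using a two-sided significance level of 0.05 and statistical power of 80%, the minimum required sample size is 44 participants per arm". Normal approximation: n = 2(1.960 + 0.842)² × (5/3)² = 43.6, so 44 per arm; 44/0.80 = 55 per arm. Both figures reproduce (the exact t-test needs 44.6 per arm, with 79.5% power at 44). They concern nitrogen balance only. No effect size, SD, correlation or power is stated for prealbumin.

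**Notation.** s0 and s5 are the prealbumin SDs at POD −1 and POD 5, ρ is their correlation, and n is the number per arm. None of s0, s5 and ρ is in the article, so ranges are assumed below.

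**Formulas (large samples).**
- t-test on change: variance = (2/n)(s0² + s5² − 2ρ·s0·s5)
- ANCOVA on baseline: variance = (2/n)·s5²(1 − ρ²)
- Difference = (2/n)(s0 − ρ·s5)² = (2/n)·s0²(1 − β)², where β = ρ·s5/s0 is the slope of POD 5 on baseline.

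The difference is never negative and is zero only when β = 1. The condition is therefore on the slope and not on the correlation alone. For example, ρ = 0.7 with s5/s0 = 1.4 gives β = 0.98 and essentially no loss.

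**Equal SDs.** The variance ratio, ANCOVA to change, is (1 − ρ²)/[2(1 − ρ)] = (1 + ρ)/2.

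| ρ (assumed) | Variance ratio | Loss, variance scale | Reduction in SE with ANCOVA | Loss in simulation, 44 per arm |
|---|---|---|---|---|
| 0.3 | 0.65 | 35% | 19% | 33% |
| 0.5 | 0.75 | 25% | 13% | 24% |
| 0.7 | 0.85 | 15% | 8% | 14% |

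The simulation (20,000 trials per row) includes the cost of estimating the slope. That cost is one to two percentage points at this sample size. Outside the range shown, equal SDs give a 45% loss at ρ = 0.1 and 5% at ρ = 0.9.

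**Unequal SDs, ρ from 0.3 to 0.7.**
- s5 = 0.8·s0: at ρ = 0.3 the ratio is 0.64 × 0.91/(1.64 − 0.48) = 0.502, a 50% loss. At ρ = 0.7 it is 0.64 × 0.51/(1.64 − 1.12) = 0.628, a 37% loss.
- s5 = 1.2·s0: at ρ = 0.3 the ratio is 1.44 × 0.91/(2.44 − 0.72) = 0.762, a 24% loss. At ρ = 0.7 it is 1.44 × 0.51/(2.44 − 1.68) = 0.966, a 3% loss.

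**Power, as illustration only.** If the t-test on change happened to have 80% power at α = 0.05, ANCOVA with equal SDs would have about 94%, 90% and 86% at ρ = 0.3, 0.5 and 0.7. At α = 0.025 the figures are about 94%, 91% and 87%.

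**Chance imbalance.** At 55 per arm the baseline difference has standard error √(2/55) = 0.19 SD. With equal SDs and ρ = 0.5, so β = 0.5, a baseline difference of that size shifts the change-score estimate by (1 − 0.5) × 0.19 = 0.095 SD, in the direction opposite to the imbalance. ANCOVA removes this shift. Averaged over randomizations the shift is zero, so it adds variance and not bias.

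**The case against.** The strongest reply is that nothing here is an error. The two-sample t-test on change is unbiased under randomization and controls type I error. No power is claimed for prealbumin, so no stated figure is contradicted, and the article calls the primary endpoint its sole confirmatory analysis. All of this stands, and it limits the point to efficiency.

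A second reply is that the detail sits in SAP v1.0, which may specify the prealbumin model further. That is possible, but Table 4 is presented as the prespecified analysis and names only t-tests. If the SAP says otherwise, Table 4 should be brought into line.

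Four stronger readings are tempting and are not supported:
- A reader might take 15–35% as a property of this trial. It rests on an assumed correlation and on equal SDs, neither of which the article gives.
- A reader might argue that the large fall in prealbumin after surgery makes the correlation low. A fall in the mean says nothing about correlation; a uniform drop leaves it unchanged.
- A reader might say that the change score over-corrects whenever the correlation is below 1. That holds with equal SDs. In general it is the slope that decides.
- A reader might count the paired tests as part of the precision loss, or assume that they will be used to claim a treatment effect. They accompany a separate between-group test and cost no precision, and the article nowhere says that a within-group p-value will support a claim.

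**Conclusion.** The point holds as an avoidable loss of efficiency on a Holm-controlled key secondary endpoint. It is not a flaw in validity. The printed analysis ignores a baseline value that the trial collects, and in large samples baseline-adjusted ANCOVA is never less precise than the change score. The direction is firm and the size is conditional: about 35% to 15% of precision on the variance scale (19% to 8% in SE) if the SDs are equal and ρ is 0.3 to 0.7, about 3–24% if the POD 5 SD is 1.2 times baseline, and 37–50% if it is 0.8 times. There is no loss if the slope is 1. The paired tests need only a statement of their role.

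**What to change.** In Table 4 and the SAP, before the coded labels are released, make the between-group test for prealbumin an ANCOVA with treatment arm as factor and POD −1 prealbumin as covariate. The outcome can be the POD 5 value or the change: with baseline in the model the treatment effect is identical, so the endpoint definition and the Holm procedure stay as they are. Report the adjusted mean difference with its 95% CI. State that the within-group paired tests are descriptive and are not evidence of a treatment effect. The same model for albumin, total protein and skeletal muscle index is optional, since these are exploratory.

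No new data or patients are needed. The cost is wording, a dated SAP revision and, where the protocol text itself changes, an amendment with IRB approval. The article expects recruitment to run until February 2027 and labels to stay coded until after database lock, so there is time to do this without sight of between-group results. The revision should record that.
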